## Statistics

### ***A description of the statistical methods to be employed, including timing of any planned interim analysis(es)***

Baseline equivalence and attrition between groups will be examined using single-level analyses; one-way analyses of variance to examine normally distributed data, Chi-square to examine binominal data, and Mann-Whitney U-test to examine non-normally distributed data. To examine intervention by time interaction effects, mixed effects regression will be used due to the multi-level and hierarchical nature of the data. To account for intracluster correlations between schools, intervention effects will primarily be examined using hierarchical linear modeling (HLM) for normally distributed data and hierarchical generalized linear modeling using Poisson sampling for count data. Outcome variables will be centered at post-test to allow for comparisons between groups immediately after the intervention and growth terms will be analysed to determine the magnitude of the follow-up effects. Analyses will be conducted using the program HLM 6 (57). If unconditional models reveal that less than 10% of systematic variance exists at the between-school level for any outcome variable, HLM will be abandoned and single-level analyses will be used (58). For these variables, ANCOVAs utilising the SPSS GLM procedure will be conducted to account for any baseline differences that might exist between groups. Bonferroni adjustments will be made for multiple comparisons. Odds ratios and 95% confidence intervals will also be calculated.

Interim analyses will take place at each assessment stage (including the baseline assessment). This will assist with the monitoring of data collection and data entry. Final stage analyses will be carried out at the 36 month follow-up.

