## Trial Design

***A specific statement of the primary endpoints and the secondary endpoints, if any, to be measured during the trial***

The implementation of Climate Schools and Preventure programs will finish by the end of Term 3 (21st September) in 2012 and the final assessment surveys will be administered by the end of Term 1 (10th April) in 2015.

***A description of the type/design of trial to be conducted (e.g. double-blind, placebo-controlled, parallel design) and a schematic diagram of trial design, procedures and stages***

This study will employ a clustered randomized controlled trial. Cluster randomization was chosen to avoid contamination of the control group. Schools will be randomly allocated to one of four groups (6 schools per group); (1) the 'Control' condition (usual classes), (2) the 'Climate Schools only' condition, (3) the 'Preventure only' condition, or (4) the 'CAP (Climate Schools and Preventure)' condition. The flow chart of allocation of schools to intervention groups is depicted in Figure 1.

Figure 1. Flow chart of allocation of schools to the intervention groups

[figure not shown]

Table 1 illustrates the stages of intervention and assessment. Baseline assessments and four follow-up assessments will be carried out over the study period. All parent consent forms will go out in the first 2-3 weeks of Term 1 (6th Feb - 17th Feb) and all Baselines (with student consent) will be implemented as soon as possible after this date (aim to finish those on March 9th - gives 3 weeks). Therefore 6 month surveys will be done in September before the end of Term 3 (with room for some to do it in Term 4).

As soon as they complete the baselines they can start the Climate intervention. Preventure will be run in Terms 2 and 3 (with a couple of schools run in Term 1 when CI [name] comes to Australia to train the clinicians).

Table 1: CAP study assessment and intervention timeline

|       | Baseline Survey (including SURPS) | Climate program      | Preventure program (high-risk students) | 6 month F/U Survey | 12 month F/U Survey   | 24 month F/U Survey   | 36 month F/U Survey   |
|-------|-----------------------------------|-----------------------------|------------------------------------------------|--------------------|-----------------------|-----------------------|-----------------------|

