### ***The number of subjects planned to be enrolled***

***In multicentre trials, the numbers of enrolled subjects projected for each trial site should be specified. Reason for choice of sample size, including reflections on (or calculations of) the power of the trial and clinical justification***

To account for cluster randomisation, sample size calculations are based on recent sample size requirements developed by Heo & Leon (2009) to detect intervention by time interactions in longitudinal cluster randomized clinical trials. This trial will be powered to detect differences in the overall sample as well as in the high-risk students also. To allow for comparisons between the high-risk students, 600 high risk students from 20 schools are required (i.e. 30 high-risk students per school and 5 schools per intervention group). This would achieve 80% power to detect a standardized between-group mean difference of 0.3 ( $p = 0.05$ ) in outcomes at the end of the trial with 7 measurement occasions. An effect size of 0.3 is comparable to previous trials of drug prevention programs (Cuijpers, 2002; Tobler & Stratton, 1997). To account for dropouts during the trial which we expect to be approximately 10% ([name] et al., 2009a; [name] et al., 2010), we aim to recruit 80 students per school, 40% ( $n = 32$ ) of whom are expected to be high-risk based on previous research CI [name], and 6 schools per group giving us a total of 1920 students from 24 schools at baseline to test the effect of the intervention in the overall group.

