***The level of significance to be used***

All tests conducted will use a predetermined alpha level of .05.

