## 4. Sample Size (Maximum of 250 Words)

Outline the intended sample size for the project and justify how this will meet the aims of the study.

Sample size calculations tools can be found online at:

- <http://powerandsamplesize.com/Calculators/> (quantitative)
- <http://stat.ubc.ca/~rollin/stats/ssize/index.html> (quantitative)
- [http://eprints.ncrm.ac.uk/2273/4/how\\_many\\_interviews.pdf](http://eprints.ncrm.ac.uk/2273/4/how_many_interviews.pdf) (qualitative)

Participants for this study are 2,190 individuals who were recruited to the original CAP study as students in 2012. Power calculations for the original trial were based on recent methods developed to account for cluster randomisation (Heo et al., 2009). These calculations assumed 20% drop-out, and indicated a total of 1,920 participants recruited from 24 schools would achieve 80% power to detect a between-group mean difference of 0.15 ( $p < 0.05$ ). For comparisons among high risk participants, 600 students from 20 schools would achieve 80% power to detect a standardized between-group mean difference of 0.3. In our original study we achieved well over this recruitment target, with 2,190 students and 947 high-risk students participating in the study.

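### Student-level tests of attrition and baseline balance between school-randomised arms hold the 5% level only if the intraclass correlation is zero

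*Protocol*

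**What the plan says.** The Trial Design section makes the school the unit of allocation: "Schools will be randomly allocated to one of four groups (6 schools per group"). In the Statistics section, the sample size paragraph plans cluster sizes: "we aim to recruit 80 students per school", with "6 schools per group giving us a total of 1920 students from 24 schools at baseline".

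The statistical methods paragraph then states: "Baseline equivalence and attrition between groups will be examined using single-level analyses". It names one-way ANOVA for normal data, chi-square for binary data, and "Mann-Whitney U-test to examine non-normally distributed data". No allowance for school is attached to any of these. The sentences that follow move to hierarchical models for intervention effects, giving correlation within schools as the reason. Later the paragraph promises Bonferroni adjustment for multiple comparisons, without saying which comparisons it covers.

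The significance level is general: "All tests conducted will use a predetermined alpha level of .05".

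On dropout, the sample size paragraph says "To account for dropouts during the trial which we expect to be approximately 10" per cent. The project description for the extended follow-up says of the same calculation: "These calculations assumed 20% drop-out". Its assessment table reports 1,601 of 2,190 students at year 3, printed as 71% retained.

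**The concern.** The paragraph recognises clustering for outcomes and sets it aside for attrition and baseline balance, although both comparisons are between arms made up of whole schools. If students in one school resemble each other in whether they complete a survey, a student-level test treats differences between schools as evidence of differences between arms. Such clustering is plausible here: surveys are scheduled by school term, and each school chooses online or paper completion. The protocol does not quantify it.

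The check at stake is attrition by arm. Loss to year 3 is well above what was planned, so readers will look to this comparison when judging bias. If the test often rejects when the arms do not differ, a positive result says little.

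A smaller, separate gap is that Mann-Whitney compares two groups and the trial has four.

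**Working it through.** **Inputs from the protocol.** Four arms, 6 schools per arm, 80 students per school, alpha .05. Total: 4 × 6 × 80 = 1,920, which matches the stated figure.

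**Input that is assumed.** The protocol gives no ICC for attrition or for any baseline variable. A range of 0 to 0.10 is used. The upper end corresponds to the protocol's own threshold of between-school variance for dropping hierarchical models of outcomes.

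**Formula.** With equal clusters and no true difference, the student-level four-arm chi-square statistic behaves approximately as DE × chi-square on 3 df, where DE = 1 + (80 − 1) × ICC. The 5% critical value is 7.815, so the actual false-positive rate is P(chi-square on 3 df > 7.815 / DE).

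Worked case, ICC 0.02: DE = 1 + 79 × 0.02 = 2.58; 7.815 / 2.58 = 3.03; P = 0.387.

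| ICC (assumed) | DE | False-positive rate, formula | Simulated, attrition 10%, 20% and 29% |
|---|---|---|---|
| 0 | 1.00 | 0.050 | 0.048–0.050 |
| 0.001 | 1.08 | 0.065 | not run |
| 0.005 | 1.40 | 0.133 | 0.132–0.134 |
| 0.01 | 1.79 | 0.225 | 0.220–0.226 |
| 0.02 | 2.58 | 0.387 | 0.380–0.392 |
| 0.05 | 4.95 | 0.664 | 0.663–0.665 |
| 0.10 | 8.90 | 0.831 | 0.834–0.837 |

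The simulation used beta-binomial dropout in 24 schools of 80, with 20,000 trials per setting. The stated .05 is reproduced at ICC 0 and only there. With 72 per school instead of 80 (10% loss), the formula gives 0.206, 0.358, 0.633 and 0.810 at ICC 0.01, 0.02, 0.05 and 0.10.

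**Continuous and skewed baseline measures** (simulated normal data, 1,500 trials per setting; rate of any positive result with no true difference):

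| ICC | One-way ANOVA | Six pairwise Mann-Whitney, each at .05 | Six pairwise, each at .05/6 | Student-level Kruskal-Wallis |
|---|---|---|---|---|
| 0 | 0.048 | 0.196 | 0.043 | 0.047 |
| 0.01 | 0.223 | 0.452 | 0.185 | 0.213 |
| 0.02 | 0.397 | 0.605 | 0.345 | 0.384 |
| 0.05 | 0.675 | 0.799 | 0.629 | 0.660 |
| 0.10 | 0.841 | 0.909 | 0.811 | 0.831 |

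Bonferroni cures the multiplicity of pairwise testing (0.196 to 0.043 at ICC 0) but not the clustering. Nor does a four-group rank test applied to individual students.

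**Check of the remedy.** An F test on the 24 school-level values (3 and 20 df) rejected in 4.3–5.3% of simulated trials for attrition and 4.3–5.8% for continuous measures, across ICC 0 to 0.10.

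**Attrition by year 3.** 1,601 / 2,190 = 73.1% retained, so 26.9% lost by the counts; the printed 71% implies 29% lost.

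**The case against.** The strongest reply is that little depends on these tests. Intervention effects are estimated primarily by multilevel models, all randomised participants are included, and missing data are left to longitudinal methods. The error produces false alarms about attrition; it does not alter the effect estimate. That stands, and it limits the weight of the point. The size is also conditional: the protocol gives no ICC, and at 0.001 the inflation is slight.

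Several stronger readings are tempting but not supported:

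- A reader might take 40–65% as the expected false-positive rate. It corresponds only to ICCs of roughly 0.02 to 0.05, which are assumed.
- A reader might blame Mann-Whitney for the attrition error. Attrition is binary and goes to chi-square, which handles four arms. Mann-Whitney concerns skewed variables only.
- A reader might call the pairwise runs unadjusted. The protocol promises Bonferroni without giving its scope, so that cannot be said.
- A reader might call baseline differences found this way artefacts. The observed imbalance is real and, after randomisation, due to chance; it is the p-value that is miscalibrated.
- A reader might infer that these tests choose the covariates. The protocol does not say so. Its ANCOVA sentence applies only where hierarchical modelling is dropped, and its wording is compatible with routine baseline adjustment.

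**Conclusion.** The point holds as a defect in a stated analysis. Single-level comparison of attrition and baseline measures between school-randomised arms does not hold the protocol's .05 level unless the ICC is zero. For attrition, with 80 students per school, the actual level runs from 6.5% at ICC 0.001 through about 22% at 0.01 to 66% at 0.05. These figures assume equal clusters and a common ICC; the result hardly depends on the attrition rate.

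The practical consequence is mainly a likely false alarm about differential dropout, in a trial whose year-3 loss of 27–29% exceeds both planning figures in the document (10% and 20%). For baseline measures the inflation is the same but matters less. The Mann-Whitney wording is a separate, smaller gap. Nothing here impugns the multilevel outcome analysis; the rule for abandoning it below 10% between-school variance is a different question.

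**What to change.** Replace the single-level sentence as follows:

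- **Attrition:** compare arms with a logistic model that has a school random effect, or with a test on the school-level proportions (24 schools planned, 26 recruited). The F test on school proportions is the version checked above; the logistic model was not simulated.
- **Baseline:** describe by arm without p-values. If skewed measures are to be tested, use Kruskal-Wallis on school summaries, which handles four groups and respects the unit of allocation.
- **Bonferroni:** state whether it covers any of these comparisons.

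This does not call for adding the baseline outcome as a covariate to the repeated-measures models. The seven measurement occasions in the sample size paragraph match baseline plus the six follow-ups listed under Assessment of Efficacy, so baseline appears to be part of the response already.

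The cost is wording only, with the same data and a type of modelling already planned. Attrition comparisons become slightly wider but correctly calibrated.

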***Procedure for accounting for missing, unused, and spurious data***

The appropriate longitudinal statistical methods will be used that account for missing data.

***Procedures for reporting any deviation(s) from the original statistical plan  
(any deviation(s) from the original statistical plan should be described and justified in  
protocol and/or in the final report, as appropriate)***

Any deviations from the original statistical plan will be described and justified in an amendment to this protocol.

***The selection of subjects to be included in the analyses  
(e.g. all randomized subjects, all dosed subjects, all eligible subjects, evaluable subjects)***

All randomised participants will be included in the overall efficacy analyses.

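### Dropping the school level for any outcome with under 10% between-school variance leaves a school-randomised trial with an inflated type I error for those outcomes

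*Protocol*

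**What the plan says.** Trial Design in the protocol makes the school the unit of allocation: "Schools will be randomly allocated to one of four groups (6 schools per group". The sample size section plans 80 students per school, of whom 32 are expected to be high-risk.

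The statistical methods section makes hierarchical linear modelling (HLM) the main method, or its generalised form for counts, expressly to deal with correlation within schools. It then adds an outcome-by-outcome exception. If the unconditional model shows "less than 10% of systematic variance exists at the between-school level for any outcome variable, HLM will be abandoned and single-level analyses will be used", the replacement is specified as follows: "ANCOVAs utilising the SPSS GLM procedure will be conducted to account for any baseline differences that might exist between groups". No school term, cluster-robust variance or cluster-based degrees of freedom is named for that replacement. Bonferroni adjustment is planned, but the number of comparisons is not given. The significance level is fixed: "All tests conducted will use a predetermined alpha level of .05".

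The efficacy assessment section only repeats that HLM will be used for clustered data. Nothing elsewhere in the protocol withdraws or limits the exception.

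**The concern.** When whole schools are allocated, the variance of an arm mean is inflated by a factor that depends on both the ICC and the number of students per school. A 10% threshold looks only at the ICC. With 80 students per school, an ICC of 0.05 multiplies the variance almost fivefold, yet the rule treats that as small enough to ignore.

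Any outcome that falls under the rule gets standard errors that are too small. The rule covers the intervention comparisons that test the trial's hypotheses, so ordinary differences between schools could be reported as programme effects.

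**Working it through.** **Inputs from the protocol.** Four arms with 6 schools each (Trial Design); m = 80 students per school, or 32 high-risk (sample size section); alpha .05 (significance level section); 10% threshold (statistical methods section).

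**Assumptions.** The test is two-sided, since sidedness is not stated. ICC values run from 0.005 to 0.09, since none is given. The undefined term for the between-school share is read as the ICC. The comparison is pairwise, before baseline adjustment and before Bonferroni.

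**Step 1: the plan's own figure.** With ICC = 0, the single-level test has error 2 × Φ(−1.96) = 5.0%. The stated alpha holds in that case only. The 80% power in the sample size section cannot be re-derived without an ICC and a within-student correlation, and nothing below depends on it.

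**Step 2: the fallback test alone.** Design effect DE = 1 + (m − 1) × ICC, and actual error = 2 × Φ(−1.96/√DE). At m = 80:

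- ICC 0.01: DE = 1 + 79 × 0.01 = 1.79; 1.96/1.338 = 1.465; error 14.3%.
- ICC 0.05: DE = 1 + 79 × 0.05 = 4.95; 1.96/2.225 = 0.881; error 37.8%. The standard error is understated 2.2-fold.
- ICC 0.09: DE = 1 + 79 × 0.09 = 8.11; 1.96/2.848 = 0.688; error 49.1%.

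**Step 3: the complete two-step rule.** The protocol keeps HLM when the estimated share reaches 10%, so the trigger has to be part of the calculation. Simulation used 20,000 trials per setting, 4 arms × 6 schools, no treatment effect and an ANOVA estimate of the ICC. The single-level test was used below 10%, and otherwise a school-level t-test on 20 degrees of freedom stood in for HLM. At m = 80:

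| True ICC | Fallback triggered | Fallback alone (formula) | Two-step rule | School-level test throughout |
|---|---|---|---|---|
| 0.005 | 100% | 9.7% | 9.9% | 5.0% |
| 0.01 | 100% | 14.3% | 14.2% | 5.0% |
| 0.02 | 100% | 22.2% | 21.7% | 4.7% |
| 0.05 | 99.4% | 37.8% | 37.9% | 5.2% |
| 0.07 | 90.7% | 44.3% | 39.4% | 5.1% |
| 0.09 | 67.4% | 49.1% | 32.7% | 5.0% |

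The last row shows why the rule's error falls after its peak. At a true ICC of 0.09 the fallback runs in 67.4% of trials with 46.0% error, which contributes 0.674 × 0.460 = 31.0 percentage points. The other trials keep the clustered test and add only about 1.7 points.

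**Step 4: smaller clusters.** With the planned 10% dropout (72 per school), the two-step rule gives 13.8% at ICC 0.01 and peaks at 37.6% at 0.07. With 32 high-risk students per school it gives 9.1% at 0.01 (8.7% by formula), 21.7% at 0.05, 22.7% at 0.07 and 20.0% at 0.09.

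**Step 5: Bonferroni.** Six pairwise tests are assumed, so the nominal level is 0.05/6 = 0.83% each. At m = 80 the two-step rule gives about 5% to 27% per test over ICC 0.01 to 0.09. Bonferroni lowers the error but leaves it several times its nominal level.

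**The case against.** The best defence is that HLM is the primary analysis and the single-level route is only conditional. No ICC is documented, the fallback adjusts for baseline, and Bonferroni applies. Much of this limits the size of the error. The residual ICC after baseline adjustment governs the error and may be lower than the raw one. At an ICC of zero there is no inflation. If the protocol's undefined variance term means something narrower than the ICC, the upper end of the range might not trigger the rule. None of this makes 10% a safe threshold at 80 students per school.

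Several stronger readings are tempting but not supported:

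- **The rule has 49% error.** That is the fallback test alone at ICC 0.09. The rule as written retains HLM in about a third of such trials.
- **The rule contradicts the sample size section.** That section says "To account for cluster randomisation, sample size calculations are based on recent sample size requirements", and HLM is primary. A conditional fallback is a poor choice, not a contradiction.
- **The ANCOVA must drop students with missing data.** The protocol does not say how the ANCOVA treats missing values. It promises that "All randomised participants will be included in the overall efficacy analyses", and imputation is not excluded.
- **The rule governs the 5- to 7-year results.** The statistical methods section places its final analyses at 36 months. The extension's ethics application gives no analysis section, and silence does not adopt the rule.
- **The single-level baseline and attrition checks, and the Mann-Whitney test, belong to the same fault.** They are minor and do not bear on error control for efficacy.

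**Conclusion.** The concern holds for the 10% rule and its single-level ANCOVA. As written, the rule removes the school level where clustering still matters. The two-step type I error is about 10% at ICC 0.005, rises to a peak near 39% at 0.07 and is 33% at 0.09, for an unadjusted two-sided pairwise test with 80 students per school. In the high-risk subset it is roughly 8-9% to 23% for ICC 0.01 to 0.09. The ICCs are assumed, and baseline adjustment may bring the figures down, but the inflation disappears only if the residual ICC is zero. The documents do not show which outcomes, if any, were analysed under the fallback. This should be corrected because it affects false-positive control on the efficacy outcomes.

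**What to change.** Delete the 10% rule and the single-level ANCOVA fallback from the statistical methods section. State that every efficacy outcome model keeps a school-level random effect, or another analysis valid for clustered allocation, with between-school degrees of freedom, whatever the estimated ICC. Baseline adjustment can stay within that model.

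The change to the text is small, since the multilevel models are already planned, and a school-level test held its error at about 5% in every setting simulated. Confidence intervals will be wider for outcomes that would have gone to the fallback. The extension's lay summary already reports 3-year results, so any outcome analysed by the single-level route would need to be re-analysed.

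### The ANCOVA fallback gives up the repeated surveys as well as the school level and has no imputation step, which conflicts as written with the protocol's missing-data and all-randomised commitments

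*Protocol*

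**What the plan says.** In the Protocol's Statistics chapter, the section on statistical methods plans mixed-effects regression for intervention-by-time effects. In that model "growth terms will be analysed to determine the magnitude of the follow-up effects". It then sets an outcome-by-outcome switch: "If unconditional models reveal that less than 10% of systematic variance exists at the between-school level for any outcome variable, HLM will be abandoned". A single-level analysis takes its place. The replacement is named: "For these variables, ANCOVAs utilising the SPSS GLM procedure will be conducted to account for any baseline differences that might exist between groups". No imputation or other missing-data step is attached to it.

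Two later statements in the same chapter carry no exception for the fallback. On missing data: "The appropriate longitudinal statistical methods will be used that account for missing data". On the analysis set: "All randomised participants will be included in the overall efficacy analyses".

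The section on the number of subjects bases the sample size on a method for intervention-by-time interactions in longitudinal cluster trials, with 7 measurement occasions and about 10% drop-out.

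**The concern.** The switch is triggered by the share of variance between schools, but it removes two things: the school level, and the longitudinal structure within students. The trigger bears only on the first. A student's surveys at successive waves remain correlated, and remain informative about the waves the student misses, however small the school share is.

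An ANCOVA in SPSS GLM uses only students with complete data on the variables in the model. Three things follow for a fallback outcome if no imputation is added:

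- Randomised students without the required surveys leave the analysis, and the other surveys they did complete go unused.
- Because the switch works outcome by outcome, different outcomes may be tested on different sets of students.
- If the ANCOVA is run separately at each follow-up, there is no intervention-by-time term, although that is the effect used to size the trial.

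The Background chapter links early drug use to early school dropout, so loss that depends on the outcome is plausible. The issue is separate from clustering: cluster-robust standard errors on the same ANCOVA would leave it untouched.

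**Working it through.** **1. The passages side by side.** The statistical-methods section says "HLM will be abandoned and single-level analyses will be used" and names ANCOVA in SPSS GLM. The missing-data section commits, without exception, to longitudinal methods that account for missing data. There are two ways to run the fallback, and the text does not choose:

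- *One follow-up on baseline.* This is not longitudinal. It keeps students who have both surveys and has no time term.
- *Repeated-measures GLM.* This can carry a group-by-time term, but it drops any student who misses any included wave.

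Neither meets the missing-data commitment without an added step.

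**2. The plan's own power figure.** For high-risk students the plan says: "This would achieve 80% power to detect a standardized between-group mean difference of 0.3". Inputs: 30 × 5 = 150 per group, difference 0.3 SD, alpha 0.05 (taken as two-sided), 7 occasions.

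- Single unadjusted time point, no clustering: Φ(0.3/√(2/150) − 1.96) = Φ(2.598 − 1.96) = 73.8%.
- Slope over 7 equally spaced occasions (t = 0 to 6, Var(t) = 4, slope difference 0.3/6 = 0.05), random intercept, SE = √(2(1−ρ)/(150 × 7 × 4)). At ρ = 0.3, SE = 0.0183 and power is 78.2%. At ρ = 0.4, SE = 0.0169 and power is 84.1%.

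The within-student correlation is not stated, so the 80% can be neither confirmed nor refuted. The point does not depend on it.

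**3. Students lost.** Counts are from Project Description section 3, Schedule of Assessments, Table 1, with 2,190 at baseline.

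| Follow-up | Surveyed | Retained | Printed | Omitted |
|---|---|---|---|---|
| 12 months | 1,818 | 83.0% | 83% | 372 (17.0%) |
| 24 months | 1,732 | 79.1% | 79% | 458 (20.9%) |
| 36 months | 1,601 | 73.1% | 71% | 589 (26.9%) |

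The printed 71% does not match its own count. Taken at face value it would mean 29% omitted. On planning assumptions the loss is 10% (Protocol, number of subjects) or 20% (Project Description section 4). The omitted share is larger still if some students with a follow-up lack the baseline value.

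**4. Repeated-measures reading.** With the 12-, 24- and 36-month waves included, the share with complete data is at most 73.1% (the smallest wave). It is at least 1 − (372 + 458 + 589)/2,190 = 35.2%. No 6-month count is given.

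**5. Possible bias (simulation; the inputs are assumptions).** Two arms, with outcomes at baseline, 24 and 36 months, all pairwise correlations 0.6. About 24% to 29% are missing at 36 months, with missingness logistic in the 24-month outcome. The estimate is the complete-case ANCOVA of 36 months on baseline.

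| Dependence on 24-month outcome, by arm | Error in estimated effect |
|---|---|
| Same slope in both arms, including 24% v 29% missing | about 0.01 SD or less |
| Slopes 1.0 v 0.8 | at most 0.016 SD |
| Slopes 1.0 v 0.3 | about 0.04 SD |
| Slopes 1.0 v 0 | about 0.06 SD |

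The sign depends on which arm has the steeper slope. Bringing in the 24-month value by arm returns the estimate to within about 0.003 SD of truth. That is true by construction, because missingness was generated from that value.

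**The case against.** The strongest objection is that the passages can be reconciled. Nothing forbids imputation before the ANCOVA, the missing-data commitment may be read as covering the fallback, and a statistical analysis plan that is not shown might supply the detail. A reader might infer that the two sections cannot both be followed, and that goes too far. What stands is that the protocol names a specific non-longitudinal method for these outcomes with no missing-data step, so followed as written it departs from its own commitment.

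A reader might also take it as stated that the ANCOVA is run one follow-up at a time, with no intervention-by-time term. The text does not say so, and a repeated-measures GLM is possible. That answers the time-term point but not the listwise deletion.

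The sentence on all randomised participants answers a prompt about the analysis set, so it can be read as an intention-to-treat statement, not a promise that every student contributes data to every model. On that reading, the conflict rests on the missing-data sentence alone.

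On harm, the Background supports drop-out related to use but not a difference between arms, and with equal dependence the bias is negligible. The safety chapter does remind students distressed by Preventure that they may withdraw, a route that exists in only two arms, but that does not establish arm-specific dependence on use. The protocol also examines attrition between groups, which would help reveal unequal loss but would not correct it.

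Finally, the 27% comes from the later extension application and was not known at planning; the planning figure is 10%.

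**Conclusion.** The point holds as an inconsistency in the analysis plan that should be corrected. The fallback condition justifies at most a change in how the school level is handled, not abandoning the repeated surveys within students. As written, it conflicts with the commitment to longitudinal methods that account for missing data and, read literally, with including all randomised participants.

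The firm consequences are lost students and unused repeated surveys. At 36 months the loss is about 10% on the planning assumption and 27% on the reported count. Under the one-follow-up reading, the intervention-by-time effect is also not tested for these outcomes. All of this assumes listwise deletion with no imputation, and applies only to outcomes that meet the 10% condition.

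A reader might infer that the fallback materially biases the results. The document does not support that. An error of 0.04 to 0.06 SD, or 13% to 20% of the 0.3 SD target, needs drop-out that depends on earlier use very differently by arm. With similar dependence it is about 0.01 SD or less.

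**What to change.** In the statistical-methods section, replace the switch to ANCOVA. For outcomes that meet the fallback condition, keep the longitudinal mixed model already planned, fitted to all available surveys, with at least a student-level random effect and with the school level also retained. If an ANCOVA is kept for any outcome, state that it follows multiple imputation done separately by arm, using all earlier surveys, and say whether it is run at one follow-up or as repeated measures.

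The cost is a wording change and slightly more analysis work; no new data are needed. Correct the printed 71% in Table 1 of the Project Description, or explain its denominator.
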